### Randomization

Patients will be randomly allocated (1:1) to groups receiving either escitalopram or TECAS. Stratified blocked randomization codes will be generated by PROC PLAN using SAS software, which will be stratified by the study site. The research assistants will use the randomization codes to produce opaque, sealed envelopes. Each envelope will be labeled with a participant-specific randomization identification number and contain a treatment allocation number. After the collection of patients’ basic information, participants will be assigned a randomization identification number by study staff. By using a central randomization system composed of free telephone, short message, and E-mail, the randomization identification number and treatment allocation will be accessed after participants received their baseline clinical evaluation. Participants, clinical psychiatrists, and treatment technicians will be aware of the treatment condition. The staff assessing treatment outcomes will be blinded to treatment condition because they will be segregated in a different clinic area. The participants’ treatment allocation will be required not to be discussed with these staff or other participants.

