### Statistical Analysis

The proportion of participants with a reduction ≥50% in MADRS from baseline was 83.3% in the TECAS group and was 80.0% in the escitalopram group in our pilot study (unpublished data). Calculated by PROC POWER in SAS, in total, 470 participants will be needed to provide 90% power to detect a difference of −10% (the non-inferior margin) between groups in the proportion of participants with ≥50% in MADRS after 8 weeks of treatment at a 1-sided significance level of 5%, assuming a 20% loss to follow-up rate. The primary outcome will be evaluated based on the per-protocol (PP) population, defined as all randomized populations without major protocol violations. The primary outcome will be assessed using a 1-tailed test at a significance level of 0.025, while secondary outcomes using a 2-tailed test at a significant level of 0.05. For the proportion of participants with a reduction ≥50% in MADRS from baseline, the Cochran-Mantel-Haenszel test, stratified by site, will be used to test a hierarchical comparison between two groups. For the change from baseline in MADRS, the longitudinal data will be analyzed by fitting linear mixed-effects models using the baseline value as a covariate and treatment, visit, and treatment-by-visit interaction as fixed effects. The same approach will be used for the other continuous variables with longitudinal data, including HAMD-17, HAMA, PSQI, and SF-36. Missing data for the primary outcome will be imputed using the multiple imputation method under the missing at random assumption. For secondary outcomes, no imputation will be performed. To assess the robustness of the primary analyses, a sensitivity analysis will be performed without multiple imputation. All statistical analyses will be performed using SAS software, version 9.4 (SAS Institute).

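### The stated robustness check, repeating the primary analysis without imputation, assumes at least as much about missing data as the primary does and cannot show that non-inferiority survives informative dropout

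*Protocol article*

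**What the plan says.** The Statistical Analysis section of the protocol article sets the primary missing-data method: "Missing data for the primary outcome will be imputed using the multiple imputation method under the missing at random assumption". It then names one check and gives its purpose: "To assess the robustness of the primary analyses, a sensitivity analysis will be performed without multiple imputation". The article mentions no analysis of the primary outcome in which missingness may depend on the unobserved value.

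The same section plans the sample size "at a 1-sided significance level of 5%, assuming a 20% loss to follow-up rate", with a non-inferiority margin of -10 percentage points, and fixes the primary analysis as a Cochran-Mantel-Haenszel test stratified by site in the per-protocol set. MADRS is collected at baseline and weeks 2, 4, 8 and 12 (Intervention Procedure). Participants, psychiatrists and treatment technicians know the allocation, and only outcome assessors are blinded (Randomization). TECAS is self-administered at home twice daily for 8 weeks (Intervention Procedure).

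**The concern.** A sensitivity analysis earns its name by relaxing an assumption on which the primary rests. Here that assumption is MAR: given what the imputation model uses, dropouts have the same week-8 response probability as those who stayed. Removing the imputation does not relax this. The unimputed analysis is unbiased only if, within arm and site, missingness is unrelated to week-8 response. If the imputation model also uses baseline and week 2/4 MADRS, the check makes the stronger assumption; if it uses only arm and site, the two assumptions coincide. In neither case is the check weaker.

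The question left untested is whether patients who leave do worse at week 8 than their observed data predict, and whether this differs by arm. That is plausible when patients know their treatment and one arm relies on sustained home use of a device. If the shortfall is larger in the TECAS arm, both analyses err towards non-inferiority, and their agreement could be reported as robustness that was never examined.

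**Working it through.** **Inputs from the protocol article.** 470 randomised 1:1, so 235 per arm. With 20% loss, 0.80 x 235 = 188 observed per arm. The pilot response rate "was 83.3% in the TECAS group and was 80.0% in the escitalopram group in our pilot study". Margin -10 points. For the test level: "The primary outcome will be assessed using a 1-tailed test at a significance level of 0.025".

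**The plan's own figure.** n per arm = (z_alpha + z_beta)^2 x [p1(1-p1) + p2(1-p2)] / (difference + margin)^2, with 0.833 x 0.167 + 0.80 x 0.20 = 0.2991 and (0.033 + 0.10)^2 = 0.01769.
- One-sided 0.05, 90% power: (1.645 + 1.282)^2 x 0.2991 / 0.01769 gives 145 per arm, or 364 in total after dividing by 0.8. Score-based and continuity-corrected versions give 370 and 400.
- One-sided 0.025: 178 per arm, or 446 in total; the other versions give 456 and 484.

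So 470 is not reproduced at the 5% level in its own sentence, but is consistent with 0.025. This does not bear on the present point. I use 0.025, the level given for the primary test.

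**Assumptions of mine.** Normal approximation; site strata ignored; 20% of the analysed set missing unless stated; the gaps between dropouts and MAR are hypothetical.

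**1. Tipping point.** Let escitalopram dropouts behave as under MAR and TECAS dropouts respond delta below it. Estimate = observed difference - 0.20 x delta, with the standard error (SE) from 188 per arm.
- Observed 83.3% vs 80.0%: SE = sqrt(0.2991/188) = 0.0399. Lower limit with no adjustment = 0.033 - 1.96 x 0.0399 = -0.045. This is the result without imputation and also under MAR imputation using arm only; both pass. Delta to reach -0.10 = (0.10 - 0.0452)/0.20 = 0.274, so about 27 points (TECAS dropouts at about 56%).
- Observed 80% vs 80%: SE = sqrt(0.32/188) = 0.0413. Lower limit = -0.081. Delta = (0.10 - 0.0809)/0.20 = 0.096, so about 10 points.

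**2. False non-inferiority at a true difference of -10 points** (escitalopram 80%, TECAS 70%). Bias = missing fraction x gap, netted across arms. P(non-inferiority declared) = Phi(bias/SE - 1.96).
- 20% missing, 25-point gap in TECAS only: completers 75%, dropouts 50% (0.8 x 75 + 0.2 x 50 = 70). Bias 0.05; SE = sqrt((0.1875 + 0.16)/188) = 0.0430; Phi(-0.797) = 0.21.
- The same with gaps of 10, 20 and 40 points: biases of 2, 4 and 8 points; probabilities 6.6%, 15.0% and 47.8%.
- 10% missing, 25-point gap in TECAS only: completers 72.5%, 211.5 observed per arm. Bias 0.025; SE = sqrt((0.1994 + 0.16)/211.5) = 0.0412; Phi(-1.35) = 0.09.
- 20% missing, gaps of 25 points (TECAS) and 15 points (escitalopram): completers 75% and 83%. Bias 0.20 x 0.10 = 0.02; SE = sqrt((0.1875 + 0.1411)/188) = 0.0418; Phi(-1.48) = 0.07.
- Equal loss and equal gaps: bias 0.

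**3. What the stated check would show.** Keep the observed rates at 83.3% and 80.0%, and let every dropout be a non-responder.
- Loss 25% TECAS, 15% escitalopram: without imputation +3.3 points, lower limit -4.5 (pass). Counting dropouts as non-responders: 0.75 x 83.3 - 0.85 x 80.0 = -5.5 points, lower limit -14.1 (fail).
- Loss 20% in each arm: non-responder difference +2.6, lower limit -6.0 (pass).
- Loss 15% TECAS, 25% escitalopram: +10.8, lower limit +2.3 (pass).

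The unimputed result is the same, to within rounding, in all three cases; the result that accounts for the dropouts is not.

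**The case against.** **The statistical analysis plan is not shown.** A reader might infer that no other sensitivity analysis is planned. The article does not say so: it describes one check without excluding others, and tipping-point analyses are ordinary content for an analysis plan. This limits the point to the check that the article itself fixes. It does not rescue that check, whose stated purpose it cannot serve. Nor does the wording literally say complete-case, though that is its natural meaning.

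**MAR imputation can already capture visible lack of effect.** A reader might infer that MAR simply makes TECAS dropouts look like average completers. If the model uses week 2/4 MADRS, someone who leaves after poor early scores is imputed like a completer with equally poor scores, and the imputed and unimputed results may then diverge. This stands. What remains untested is the part of dropout that the observed scores do not explain.

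**The direction of bias is not known.** A reader might infer that dropout must favour TECAS. The document does not support that: its only related evidence, in the Introduction, is poor adherence to antidepressants. Equal loss with equal gaps gives no bias, and heavier loss on escitalopram can reverse it.

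**Twenty percent may overstate the imputed share.** The figure is loss among those randomised, and per-protocol exclusions may remove some dropouts before imputation. This stands, which is why a 10% case is shown. Exclusion does not test informative dropout either.

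**Secondary outcomes.** From "For secondary outcomes, no imputation will be performed" a reader might infer a like defect in HAMD-17 response and remission. Leaving binary secondary outcomes unimputed is a common choice and largely a matter of preference. The continuous scores are analysed by mixed models, which use partial data under MAR.

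**Conclusion.** The point holds for the check that the article names. An analysis without imputation rests on a missingness assumption equal to or stronger than that of the MAR primary, so agreement between the two would say nothing about dropout that depends on the unseen week-8 outcome. The primary analysis itself is not invalidated.

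The possible size runs from nothing to material. The tipping gap is about 27 points at the pilot rates but only about 10 if the arms respond equally. False non-inferiority at a true -10% is about 21% with a 25-point gap confined to TECAS and 20% missing, and 7% to 9% under the two milder assumptions. All of these rest on hypothetical gaps, loss splits and missing fractions; they are not predictions of what will happen. Confidence is high in the logical point and necessarily lower in any single magnitude.

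**What to change.** Keep multiple imputation under MAR as the primary method and state that the model uses baseline and week 2/4 MADRS, site and arm. Make the stated robustness check a delta-adjusted tipping-point analysis: vary the imputed response probability separately in each arm over a range fixed in advance, up to all missing TECAS patients counted as non-responders, and report the delta at which the lower limit crosses -10%. Keep the analysis without imputation as descriptive only, and do not present its agreement with the primary as evidence of robustness.

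The cost is a change of wording and some extra programming, with no new data. The sponsor also accepts that the robustness statement may turn out less favourable.

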## Discussion

This study uses a non-inferiority design to compare the effectiveness of TECAS and escitalopram for depression with large sample size. This design approach will help us to determine whether TECAS, a novel therapeutic method, is clinically equivalent to the current standard first-line antidepressants with fewer adverse events.

The response rate that will be determined by MADRS is chosen as the primary outcome. The well-established MADRS is one of the most widely used scales in psychopharmacological drug research (39). The scale is less influenced by adverse patient personality traits and more focused on the assessment of core depressive symptoms, which can respond well to changes in depression severity (46). Also, we will use the HAMD-17, a scale with a high degree of recognition, as a secondary outcome to assist in evaluating the severity of depression. Insomnia and anxiety accompanying depression, and quality of life will be assessed as well. This allows for a more comprehensive comparison of the differences between TECAS and escitalopram in terms of treatment effects. In addition to comparing the therapeutic efficacy at the treatment endpoint, a 4-week follow-up period is established. This is used to compare the difference between TECAS and escitalopram in terms of the durability of the treatment effect.

There are some limitations to this trial. Firstly, it is almost impossible to blind patients and therapists due to the huge operational variability between drug treatment and TECAS. However, this trial will be blinded to the assessor to minimize the potential for bias. Secondly, as TECAS is a novel fusional treatment, its application lacks widely used, or standardized, optimal parameters, such as frequency, amperage, and duration. We expect the results of this trial to demonstrate the potential of TECAS as an optional treatment for depression in the future, and further confirm the optimal parameters and optimize its treatment outcomes in subsequent applications and studies.

## Ethics Statement

The studies involving human participants were reviewed and approved by the Human Research Ethics Committees at The University of Hong Kong Shenzhen Hospital (Approval Number 2019044; approved 28 February 2019). The patients/participants have to provide their written informed consent to participate in this study.

## Abbreviations

AE: adverse events
HAMA: hamilton anxiety rating scale
HAMD-17: 17-item hamilton depression rating scale
HKU-SZH: University of Hong Kong Shenzhen Hospital
ICD-10: international classification of diseases 10th edition
iVNS: implantable vagus nerve stimulation
MADRS: montgomery-åsberg depression rating scale
MCID: minimal clinically important difference
MDD: major depressive disorder
PSQI: Pittsburgh sleep quality index
SAE: serious adverse event
SF-36: short form 36 health survey
SNRI: serotonin and norepinephrine reuptake inhibitors
SPIRIT: standard protocol items: Recommendations for intervention trials
SSRI: selective serotonin reuptake inhibitor
SUSAR: suspected unexpected serious adverse reaction
TEAS: transcutaneous electrical acupoint stimulation
TECAS: transcutaneous electrical cranial-auricular acupoint stimulation
tVNS: transcutaneous vagus nerve stimulation
VNS: vagus nerve stimulation.
